**6.2.2 Referral for counselling:**

This will be arranged by the specialist physician, to a counsellor at their clinical centre. The counselling process will assist the participant in the following issues:

- psychological and social implications of HIV infection
- who to inform and what to say
- implications for sexual partners
- avoidance of risk to others in future

**6.2.3 Informing the General Practitioner**

The participant will be encouraged to do this, but the decision will remain at the discretion of the individual.

**6.2.4 Immunological follow-up**

Follow-up of HIV infected individuals who have received study vaccine products will be determined by the Operational Sub-Group. The intensity of assessments will be dependent both on the number of immunisations received by the individual and their clinical progress, including changes in surrogate markers such as viral load and CD4 count.

**6.3 Social discrimination as a result of a post-vaccine response**

The aim is to minimise the possibility of social discrimination in participants who develop a positive HIV-ELISA test by providing HIV testing and certification for participants as required, outlined above, both during and after the trial. In addition, an identification card stating that the individual has participated in a vaccine trial, with a contact number in case of medical emergency, will be provided.

In the unlikely event that a participant suffers social discrimination as a result of a post-vaccination response, the clinical investigators will assist the participant.

**7 Management of the trial****7.1 Data management at the Clinical Centre**

Staff at the clinical centres will be responsible for:

- Entering relevant information (see section 7.5) in the clinical notes, and holding a record for each participant which includes the CRFs with any changes made signed and dated
- The accurate completion of the case record forms
- The prompt return of the completed forms to the MRC CTU/INSERM U593 CTU
- Notification of SAEs as soon as they become aware of the event to the MRC CTU/INSERM U593 CTU

Data will be recorded directly onto the CRFs, which will provide the majority of source data for the trial. There will be some additional source data in the clinical notes, such as medical history related to eligibility, dates of visits including immunisation, results of pregnancy tests, and details of clinical management (description of adverse events and concomitant medication).

CRFs will be supplied by the data management centres and these will be forwarded for data entry after completion according to standardised operating procedures. Copies of laboratory reports containing the results of routine haematology, chemical pathology and immunology may be sent instead of completing these sections of the CRF, provided they are clearly labelled with the trial number and the date of collection. A member of the clinical trial team must sign the laboratory report. In the event of an abnormality, an indication should be given whether or not action was taken, the date of review and the signature of the clinician reviewing the result.

Changes to the CRF should be signed and dated, including changes made before the form is returned to the data management centre.

CRFs and clinical notes should be kept in a secure location for 2 years after the last approval of a marketing application or until 2 years have elapsed since formal discontinuation of product development, and at least 10-15\* years after the clinical trial has ended.

\* as per local regulations

## **7.2 Data management in the immunology laboratories**

Standardised operating procedures will be followed in all laboratories to ensure the quality of the data. Data will be stored electronically in an agreed format and datafiles transferred to the data management centres for the main analysis.

## **7.3 Data management at the MRC CTU & INSERM U593 CTU**

MRC CTU/INSERM U593 CTU will share responsibility for:

- Design of the CRFs in collaboration with the Investigators
- The database applications that will contain the computerised trial data
- Data entry for the clinical trial other than the immunologic assays
- Monitoring the trial according to ICH GCP guidelines including monitoring vaccine accountability, and dispatch and arrival of immunological specimens
- Preparation of reports to assist the monitoring
- Holding a record for each participant which contains the copy of the CRF and documentation detailing all the changes made subsequent to monitoring visits, queries raised and how they were addressed
- Coordination of the committee and group meetings (section 7.6 and 7.7) in collaboration with the Investigators
- Development of the analysis plan and conducting the analyses
- Preparation of the analysis files from the database prior to analyses
- Coordination of the final report

All CRFs and laboratory reports returned to the data management centres will be reviewed by the Data Management Team, according to standardised operating procedures. CRFs will be checked for completeness and passed for review by the Medical Experts or their deputies if required. Data will be entered onto a computerised database. Consistency checks and range checks will be performed.

The accuracy of data entry will be checked according to standardised operating procedures at each data management centre.

The data manager or their deputy will review adverse events, as they arise. Queries raised will be directed to the investigators at the relevant clinical centre by letter, fax, email or at a monitoring visit.

Prior to analysis, the safety data will be checked, adverse events validated and data extracted in order for the trial statisticians to run the analysis and prepare the tables.

Once each CTU will have a complete and final set of data from their affiliated clinical centres, these two datasets will then be merged at INSERM U593 CTU.

## **7.4 Monitoring by MRC CTU & INSERM U593 CTU**

Staff from the data management centres will visit the clinical centres they are responsible for to validate trial data held on the database against the clinical records. The site Principal Investigator and participants, by giving consent, agree that the MRC CTU/INSERM U593 CTU may consult and/or copy source records (clinical notes and laboratory values) in order to do this. Such information will be treated as strictly confidential and will in no circumstances be made publicly available. The monitoring will adhere to ICH Good Clinical Practice guidelines. The following data should be verifiable from source documents:

- documentation of any existing conditions or past conditions relevant to eligibility
- signed consent
- dates of visits including dates of immunisations

- a sample of reported laboratory results
- grade 3 or 4 adverse events and any events leading to discontinuation of the immunisation schedule
- concomitant prescribed medication

Vaccine returns will also be monitored at visits to the clinical site.

## 7.5 Data Ownership

The data generated in this study will be the property of the EuroVacc Foundation, the ANRS and the Investigators involved in the conduct of this trial and the combined database will be held on their behalf by one or both data management centres. If data are required at an earlier date for the purposes of regulatory submissions, a request should be made to the Trial Coordinating Committee.

## 7.6 Trial Coordinating Committee (TCC)

The supervision of the trial will be responsibility of the Trial Coordinating Committee (TCC). The committee has an independent chair, [name], and the voting members will include the two Chief Investigators involved in the conduct of this trial, and one further independent member. Representatives from EuroVacc and ANRS, from Imperial, Klinikum-UREG, ANRS centres and other additional non-voting members will attend as appropriate to the contents of the meeting. This committee will be responsible for final decisions about grade of adverse events and relationship to study vaccine. Notes of meetings will be kept, and these will be filed with the Sponsors.

The trial may be terminated by this Committee for any reason, including on the recommendation of the DSMC.

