**EuroVacc centres - [contact] [contact]**  
**ANRS centres - [contact] [contact]**

An analysis plan will be developed by these two institutions in collaboration with all the participating investigators.

The EuroVacc trials are overseen by a Trial Coordinating Committee (TCC). The committee has an independent chair, [name], and two other independent members. The two Chief Investigators listed on this protocol will represent the EuroVacc/ANRS investigators and have voting rights on this committee. Additional non-voting members may attend as appropriate to the contents of the meeting. This committee will be responsible for final decisions about grade of adverse events and relationship to study vaccine, and will be determined by the evolution of the adverse event.

An entirely independent Data and Safety Monitoring Committee has been appointed to review the design and protocol, and will meet on one occasion during the trial, to review the safety data, after half the participants have completed the immunisation regimen and passed week 28. Using this dataset the investigators will review the pooled immunogenicity data blind to allocation and, if less than 60% of participants have ELISpot responses, then the DSMC will be asked to review the immunogenicity by allocation as well as the safety data, and make a recommendation based on the upper confidence bound of the difference between the two groups (DNAX3 – DNAX2). The members of this committee are:

|                         |                                          |
|-------------------------|------------------------------------------|
| [name]           | Chair and infectious diseases specialist |
| [name] [name]     | Clinical Epidemiologist                  |
| [name]      | Clinical Immunologist                    |
| [name] [name] | Biostatistician                          |

There will be an additional meeting if 3 or more participants experience an unexplained, unexpected grade 3 or 4 clinical or laboratory event (confirmed on attendance or repeat testing) not resolved within 72 hours and considered probably or possibly related to vaccine product.

Screening will not commence until the approvals appropriate to the clinical centre according to ICH GCP have been obtained.

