### **3.8 Unblinding procedure**

This is an open trial for clinical investigators and participants.

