### 7.6.1 Operational sub-Group (OSG)

This group will oversee the day to day running of the trial and the members will be primarily the clinical and data management teams. The immunologists will join if there are relevant items on the agenda, but care will be taken to ensure they are not unblinded to allocation. Notes will be taken and will form the basis of the progress report to the Trial Coordinating Committee.

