### 8.2 Primary analysis

The immunological end-points will be considered present or absent according to standardised operating procedures which take the background activity into account ( $> 4$ -fold the negative control and  $> 55$  Spot forming units/ $10^6$  cells). In both EV01 and EV02, a small proportion ( $<5\%$ ) of subjects showed persistent IFN $\gamma$  ELISpot reactivity to peptide pools prior to vaccination and subsequently across several timepoints. Subjects with IFN $\gamma$  ELISpot reactivity to peptide pools prior to vaccination will be considered to have non-specific cross-reactive responses to the peptide pools, and will be excluded from the immunogenicity analysis. The two groups DNAX2 and DNAX3 will be compared in terms of the proportion responding to *env* plus *gag/pol/nef* using a Chi-square test.

All safety end-points will be graded by the Clinical Investigators and reviewed by the Operational Sub-Group. Any queries about grade and relationship to study product that cannot be resolved will be referred to the Trial Coordinating Committee for a final decision. For the primary analysis of safety endpoints (as defined in section 1.5.1), results will be expressed as a proportion and the two groups compared using Fisher's exact test.

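### Sections II and 7.6 disagree on how many independent members vote on the Trial Coordinating Committee, and no masking is stated for the contested adverse event grades it decides

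*Protocol*

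**What the plan says.** **Membership.** Section II (Summary of Trial) describes a TCC with an independent chair "and two other independent members", and adds: "The two Chief Investigators listed on this protocol will represent the EuroVacc/ANRS investigators and have voting rights on this committee". Section 7.6 also has an independent chair, but there "the voting members will include the two Chief Investigators involved in the conduct of this trial, and one further independent member".

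**Scope.** Section 7.6 states: "This committee will be responsible for final decisions about grade of adverse events and relationship to study vaccine". Section II gives it the same responsibility. Section 8.2 is narrower: the Clinical Investigators grade, the Operational Sub-Group reviews, and only queries "that cannot be resolved will be referred to the Trial Coordinating Committee for a final decision".

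**Masking.** Section 3.8 states: "This is an open trial for clinical investigators and participants". Section 1.2.1 agrees and keeps only laboratory staff blind. For the Operational Sub-Group, section 7.6.1 says "the members will be primarily the clinical and data management teams"; it takes care over unblinding for the immunologists only. No section says whether safety queries are decided with or without the allocation.

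**Endpoint.** Three of the four primary safety parameters in section 1.5.1 are defined by grade 3 or above. The fourth is a vaccine-attributable event that ends the immunisation schedule. Section 8.2 compares the groups by Fisher's exact test.

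**The concern.** A protocol should give one answer to who takes the final decision on data that define a primary endpoint. Here the two descriptions of the committee differ by one independent member, and with it goes the independent majority. A 2-2 split is possible under section 7.6 if the chair votes, and no tie-break is given.

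Investigators and participants have to be unmasked in this design. A final decision on a disputed grade does not have to be taken with the allocation in view. Some of the grading is opinion. Under section 4.1.1 and Appendix 4, induration after an intramuscular injection is grade 3 if the clinician thinks it arose in the muscle, but is graded by diameter and duration if put down to leakage into the skin layers. One such opinion can decide whether a participant counts in the primary safety comparison. If the voter knows the arm, expectations about a regimen can tilt borderline calls in one direction.

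**Working it through.** **Step 1: votes.** The protocol prints no vote shares; these are counted from the two descriptions.

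| | Section II | Section 7.6 |
|---|---|---|
| Independent chair | 1 | 1 |
| Other independent members | 2 | 1 |
| Chief Investigators | 2 | 2 |
| Chief Investigators' share, chair votes | 2/(1+2+2) = 2 of 5 (40%) | 2/(1+1+2) = 2 of 4 (50%) |
| Chief Investigators' share, chair does not vote | 2/(2+2) = 2 of 4 (50%) | 2/(1+2) = 2 of 3 (67%) |

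The sections disagree whether or not the chair votes. Independents have a majority only under section II with a voting chair.

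**Step 2: route of a grade to the endpoint.** Investigator grades; Operational Sub-Group reviews; an unresolved query goes to the TCC (8.2); grade 3 or above counts in three of the four parameters (1.5.1); the proportions go into the Fisher test (8.2). Relationship enters 1.5.1 only through the fourth parameter. It also enters the safety row under the secondary questions in section III, which leaves out events judged unrelated.

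**Step 3: what one regraded participant can do.** Two-sided Fisher's exact test, 70 per arm (section II). The event counts are illustrative and come from no document; the 0.05 level is an assumption, since section 8.2 gives none for safety.

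| Participants with an event | p | One more in the second arm | p |
|---|---|---|---|
| 0 v 5 | 0.058 | 0 v 6 | 0.028 |
| 1 v 7 | 0.063 | 1 v 8 | 0.033 |
| 2 v 9 | 0.055 | 2 v 10 | 0.031 |

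Further from the threshold, one regrade decides nothing: 0 v 2 gives 0.50, 0 v 3 gives 0.24, 2 v 5 gives 0.44.

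**Step 4: can the allocation be withheld?** By the table in section II, both arms receive the same product at weeks 0, 4 and 24, which is three of each arm's four immunisation occasions. They differ at week 8 (group 1 only) and week 20 (group 2 only). An event after a shared occasion can be described without showing the arm. An event after week 8 or week 20 cannot be reliably disguised.

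**The case against.** **Who knows the allocation.** A reader might infer that everyone who settles a grade knows the arm. The documents do not support that. Openness is stated for participants and investigators, which covers the graders and the two Chief Investigators. Nothing says that the independent chair or members see the regimen.

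**Little reaches the TCC.** Under 8.2 it sees only unresolved queries. Participants grade their own pain and systemic symptoms, many laboratory grades follow numeric limits, and other grade 3 events must be confirmed on examination or repeat testing. This stands: masking the TCC leaves most grading as it is, and nothing indicates how many queries would arise. The queries that do arrive are, however, the disputed ones.

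**Relationship.** A reader might also infer that relationship decides the primary safety endpoint generally. In 1.5.1 it decides one parameter of four.

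**Masking and section 5.2.** The relationship categories rest on timing, continuing use and reappearance on further use. Removing all immunisation dates would defeat them. This stands, so the exposure history has to stay for relationship queries.

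**Size.** The p-values near 0.05 were picked to show sensitivity. The only earlier grade 3 figure in the protocol is none reported in EV01, where 20 of 24 volunteers were allocated NYVAC, so counts may be too low for a regrade to matter. This stands; the figures are illustration only.

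**Other oversight.** A fully independent DSMC reviews safety, and suspected related serious events get multi-disciplinary review. Neither is given the final decision on grade. A committee charter or the SAP might provide for masking, but neither would remove the contradiction within the protocol.

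**Voting.** A 2-2 tie would not give the Chief Investigators control, and the wording in 7.6 leaves the list of voters open. Both are true, and both are reasons to write the rule down.

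**Conclusion.** The point holds in a limited form. Sections II and 7.6 contradict each other on the number of independent members, leave the chair's vote unstated, and describe a wider role for the TCC than 8.2 does. The Chief Investigators' share is 2 of 5 or 2 of 4 if the chair votes, which is an assumption, and 2 of 4 or 2 of 3 otherwise. The protocol states no masking for the contested grades that the committee decides, although grade 3 or above defines three of the four primary safety parameters.

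The effect on the result cannot be sized from the document, because neither the number of queries nor the expected event counts are given. One regrade can cross 0.05 when the counts lie near that level and is immaterial otherwise. The case for change is that the contradiction needs correcting anyway and the protection costs little, not that bias has been shown.

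The contradiction may be a missed carry-over: the change log for version 3.0 records updated TCC members for section 7.6 and no TCC change for the Summary.

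**What to change.** 1. Give the same voting membership in II and 7.6, and say whether the chair votes.
2. Give II, 7.6 and 8.2 the same scope: the TCC decides only unresolved queries.
3. Send grade queries to the TCC without the allocated regimen: event description, measurements, and time since the most recent immunisation.
4. For relationship queries, keep the exposure history that section 5.2 needs.
5. Let only the independent members vote on both kinds of query. If the 7.6 membership is kept and the chair votes, two voters can split 1-1, so name a tie-break.
6. Record each decision before any by-arm safety comparison.

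Cost: wording in three sections and a short query form, with the existing committee and no extra staff. What remains: events after weeks 8 and 20 stay identifiable, relationship queries stay partly unmasked, and grading by investigators and participants stays open.

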### 7.6.1 Operational sub-Group (OSG)

This group will oversee the day to day running of the trial and the members will be primarily the clinical and data management teams. The immunologists will join if there are relevant items on the agenda, but care will be taken to ensure they are not unblinded to allocation. Notes will be taken and will form the basis of the progress report to the Trial Coordinating Committee.

## 7.7 Data and Safety Monitoring Committee (DSMC)

An entirely independent Data and Safety Monitoring Committee has been appointed to review the design and protocol, and will meet on one occasion during the trial, to review the safety data, after half the participants have completed the immunisation regimen and passed week 28. Using this interim dataset the investigators will review the pooled immunogenicity data blind to allocation and, if less than 60% of participants have ELISpot responses, then the DSMC will be asked to review the immunogenicity by allocation as well as the safety data, and make a recommendation based on the upper confidence bound of the difference between the two groups (DNax3 – DNax2). The members of this committee are:

|                         |                                          |
|-------------------------|------------------------------------------|
| [name]           | Chair and infectious diseases specialist |
| [name] [name]     | Clinical epidemiologist                  |
| [name]      | Clinician                                |
| [name] [name] | Biostatistician                          |

### 7.7.1 Indications for additional review

There will be an additional meeting if 3 or more participants experience an unexplained, unexpected grade 3 or 4 clinical or laboratory event (confirmed on attendance or repeat testing) not resolved within 72 hours and considered probably or possible and likely to be related to vaccine product.

### 7.7.2 Indications for discontinuation of immunisations in all participants

If 3 or more participant experience grade 3 or 4 adverse events attributed to the same product, then further recruitment to the Clinical Trial and immunisations with that product will be discontinued pending an unblinded review of all safety data by the

DSMC. Following this review the DSMC will make a recommendation to the Trial Coordinating Committee about continuation of the trial. The sponsors will formally decide to terminate or not the clinical Trial.

## 8 Statistical considerations

Analyses will be conducted according to a modified intention to treat principle, in which all randomised volunteers that received at least one immunisation will be included. Volunteers with IFN $\gamma$  ELISpot reactivity to peptide pools prior to vaccination will be excluded from the analysis of the immunogenicity outcomes.

